#### Data analysis

In order to meet stakeholder deliverables, analyses will be completed at 2 time points: 1) analysis of 3 month data once all 3 month data have been collected, and 2) analysis of 6 month data at study end. Health care administrative data will only be analyzed after study end.

##### Primary and secondary analyses

Baseline descriptive statistics will be generated overall, between treatment groups and between recruitment settings. Employment status and medication use will be described at baseline and 3 months. Prior 3-month health care utilization assessed with the CSRI (and validated with health administrative data when available) will be described at baseline and at 3 months. All primary and secondary outcomes will be described at baseline and 3 months, including the RAS-r and CIQ subscales. In addition, at baseline and 3 months, we will describe the proportion of participants with PHQ-9 and GAD-7 scores of 10 or more, indicative of clinically important levels of depression and anxiety [40], respectively. At 3 months, we will describe clinically important cutoffs on the PHQ-9 and GAD-7 including a reduction of 5 or more points from baseline (clinically meaningful change), reduction in score of 50 % or more from baseline (response), and a score less than 10 (remission) [40]. Adverse event descriptive data will be reported at 3 months, and again at 6 months for the BWW extension group. BWW satisfaction descriptive data will be reported at 3 months for ITG participants and 6 months for DTG participants.

The primary outcome, RAS-r at 3 months, will be analyzed with an intent-to-treat analysis using an ANCOVA controlling for baseline RAS-r score as well as treatment group, unadjusted and adjusted for baseline PHQ-9, baseline GAD-7, age, sex, education, relationship status, household income, duration of episode, and recruitment setting. In sensitivity analysis, we will repeat this using a marginal structural model to account for attrition.

The same analysis will be repeated for all secondary outcomes at 3 months controlling for baseline score and treatment group. Analysis of 3 month data will be completed after all 3 month data have been collected.

In the subset of ITG participants who opt in to the nested extension study, we will examine outcomes at 6 months between treatment groups. Analysis of primary and secondary outcomes will be repeated as described above, controlling for scores at both baseline and 3 months.

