#### Allocation and blinding

At enrollment, a 2:1 allocation ratio will be used to randomize participants to ITG or DTG. This allocation ratio was chosen to immediately provide the intervention to more participants and increase likelihood of participation. Participants and providers will not be blind to treatment group. Randomization sequences will be generated independently and will be stratified by site and recruitment setting. Allocation sequence will be concealed until after baseline data has been collected to blind those involved in recruiting and consenting procedures. Group allocation will be revealed by phone or email. At t = 3 months, ITG participants who opt in to the nested study arm, will be randomized 1:1 to a 3 month BWW extension (ITG-e) or no extension (ITG-n). Group allocation will again be revealed via phone or email. The nested treatment extension arm will be concealed from participants at enrollment to encourage maximal usage of the intervention during the first 3 months. All data analyses will be blinded.

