##### Treatment as usual + BWW (months 0–3 for ITG, months 4–6 for DTG and ITG-e)

Participants will receive a 3-month subscription to BWW, free of charge. Use of BWW is participant-driven, with the ability to utilize the services at any frequency. A unique BWW access code will be emailed to participants. If registration has not occurred within 3 days of receipt, a follow-up call will be made to remind the participant to log in. For the DTG participants, a study team member will contact them 3 months after enrollment to remind them that their access to BWW will start ﻿and the access code will be emailed. Participants randomized to ITG-e will be able to reactivate their same account once allocation has been revealed.

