#### Adverse events

There is a growing consensus that adverse events (AEs) need to be evaluated in behavioural intervention trials [38, 39], as there is a theoretical risk of deterioration, especially if online self-help tools are misunderstood or not properly applied [38]. We will compare pre-defined AEs (see Table 2) between the ITG and DTG participants at 3 months, and the ITG-e and ITG-n participants at 6 months for clinically important differences that may be a result of BWW. Moreover, an independent data safety and monitoring board (DSMB) comprised of three content and methodology experts assembled for this trial will review available AE data at two interim time points: after the first 150 participants have completed 3 months, and again after 500 participants have completed 3 months, to determine if any investigation is required and if the trial is safe to continue. Health administrative data will not be available within this timeframe and will not be reviewed by the DSMB. DSMB terms of reference are available from the study investigators.

**Table 2 Tab2:** Adverse Events

Adverse Event	Measure	Description
Mental health Hospitalization	CSRI; Health administrative data	Number of hospitalizations on a psychiatric unit
Mental health ED visit	CSRI; Health administrative data	Number of ED visits for a mental health reason
Crisis service use	CSRI	Number of times using crisis supports
Increased suicidal ideation	PHQ-9 item 9	Increase in PHQ-9 item 9 score
Death	Health administrative data	All-cause mortality
Worsening depression or anxiety	PHQ-9, GAD-7	Increase in PHQ-9 or GAD-7 score over the prior 3 months
Declining social and community integration	CIQ	Decrease in CIQ score over the prior 3 months
Worsening disability	EQ-5D-5 L	Decrease in EQ-5D-5L scores over the prior 3 months
Medication discontinuation	Author question added to CSRI	Self-reported discontinuation of psychotropic medication without provider knowledge

*CSRI* client service receipt inventory, *PHQ-9* personal health questionnaire, 9-item, *GAD-7* generalized anxiety disorder questionanire, 7-item, *CIQ* community integration questionnaire, *EQ-5D-5 L* Euro-QOL quality of life measure

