##### Power calculation

We have performed a power calculation assuming a sample size of 1000 participants which is the minimum target recruitment desired by the funder. Using data from other recent studies of internet based mental health interventions [10], we have calculated power assuming a conservative 30 % attrition rate. The minimal detectable difference between the two treatment groups was calculated assuming an ANCOVA analysis with a 0.8 correlation between baseline and 3-month follow-up RAS-r measurements. With a sample size of 700 accounting for attrition, allocated in a 2:1 ratio, using an alpha of 0.05 and power of 0.9, we are able to detect a difference of 1.35 on the RAS-r.

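### Adverse events during the delayed group's own BWW period (months 4–6) enter no stated report, so about 26–33 % of planned first exposures are missing from the safety description

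*Protocol article*

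**What the plan says.** The section on treatment as usual plus BWW sets out who has access and when: "months 0–3 for ITG, months 4–6 for DTG and ITG-e". For DTG, months 4–6 are therefore the first and only period on BWW.

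Table 1 schedules the RAS-r, PHQ-9, GAD-7, CIQ, EQ-5D-5L and adapted CSRI at baseline, 3 months and 6 months, with no restriction by group. It does restrict by group where that is meant: satisfaction is marked for ITG at 3 months and for DTG at 6 months.

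Two places fix which adverse events are examined. The Adverse events section announces comparisons "between the ITG and DTG participants at 3 months, and the ITG-e and ITG-n participants at 6 months". The section on primary and secondary analyses states: "Adverse event descriptive data will be reported at 3 months, and again at 6 months for the BWW extension group". The sentence after that one assigns satisfaction data to DTG at 6 months, which is the only 6-month result named for that group. The 6-month outcome analysis is also limited to the extension: "In the subset of ITG participants who opt in to the nested extension study, we will examine outcomes at 6 months between treatment groups".

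**The concern.** The Adverse events section justifies collecting these events by the possibility that online self-help makes some people worse, especially when the tools are misunderstood or misapplied. That possibility plausibly bears on people meeting the platform for the first time. First-time use happens in two places in this design: ITG in months 0–3 and DTG in months 4–6. Only the first is assigned to a safety report.

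For DTG, the only adverse events assigned to a report come from the three months without BWW. The only BWW users whose events are reported after month 3 are those in the extension. They have already had three months of access and, as the Limitations section says, selected themselves. They do not stand in for a second set of first-time users.

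At stake is the completeness of the safety description, not the validity of the main comparison.

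**Working it through.** **Step 1: set the text side by side.**

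| Group and period | BWW access | Survey measures scheduled at period end | In the stated comparison | In the stated descriptive report |
|---|---|---|---|---|
| ITG, months 0–3 | first | yes | yes | yes |
| DTG, months 0–3 | none | yes | yes | yes |
| ITG-e, months 4–6 | continued | yes | yes | yes |
| ITG-n, months 4–6 | none | yes | yes | depends on what is meant by extension group |
| ITG not opting in, months 4–6 | none | yes | no | no |
| DTG, months 4–6 | first | yes | no | no |

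On either reading of extension group (ITG-e alone, or both re-randomized groups), DTG is outside it. DTG in months 4–6 is the only period on BWW that neither statement covers.

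**Step 2: would the data exist?** Table 2 lists nine adverse events. Eight have a survey measure (CSRI, PHQ-9, GAD-7, CIQ or EQ-5D-5L), and all these instruments are scheduled at 6 months. Death alone rests only on health administrative data. Table 2 defines the worsening of depression or anxiety, community integration and disability over the preceding three months, so those definitions fit DTG months 4–6 unchanged.

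**Step 3: inputs for the size.**
- Allocation (Allocation and blinding): "a 2:1 allocation ratio will be used to randomize participants to ITG or DTG".
- Planned number (Power calculation): "assuming a sample size of 1000 participants which is the minimum target recruitment desired by the funder".
- Attrition (Power calculation): "we have calculated power assuming a conservative 30 % attrition rate".

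**Step 4: reproduce the plan's own figure.** Evaluable number = 1000 × (1 − 0.30) = 700, which matches the Power calculation. The detectable difference given there cannot be checked without a standard deviation for the RAS-r, but it plays no part in this point.

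**Step 5: share of first exposures left out.** Share = DTG exposed / (ITG exposed + DTG exposed).
- As randomized: ITG = 1000 × 2/3 = 667 and DTG = 1000 × 1/3 = 333. Share = 333/1000 = 33.3 %.
- 30 % attrition in both arms: ITG = 467 and DTG = 233. Share = 233/700 = 33.3 %.
- 30 % of DTG lost before crossover, all ITG counted as exposed: DTG = 333 × 0.70 = 233. Share = 233/(667 + 233) = 233/900 = 25.9 %.

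**Step 6: sensitivity to loss after month 3.** The 30 % is stated for the 3-month analysis. If DTG's 233 fall by a further 15 % by month 6, the share is 198/(198 + 467) = 198/665 = 29.8 %. With a further 30 %, it is 163/(163 + 467) = 163/630 = 25.9 %. A 40 % loss of DTG before crossover, more than the protocol assumes, with all ITG counted, gives 200/(667 + 200) = 200/867 = 23.1 %.

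**The case against.** The strongest reply is that the two comparisons named are the two randomized ones. The stated purpose is to look for differences attributable to BWW, and DTG has no concurrent control after month 3, as the Limitations section discloses. Several Table 2 events are any movement of a score in the wrong direction, so a DTG before-after table will largely show natural course and random fluctuation. This stands as a limit on what the added tables can show. It does not justify leaving DTG out of the sentence in question, because that sentence promises description, not comparison.

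A second reply is that the Data analysis section promises analysis of 6-month data at study end, that the sentence does not say only, and that a fuller protocol or analysis plan may list more tables. The first is a statement of timing and names no DTG analysis. As for the rest, the article does not leave the matter open: it names the 6-month adverse-event population in two places, and DTG is in neither.

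A third reply is that the monitoring board reviews whatever adverse-event data are available, so it may see some early DTG events after crossover. That may be so, but both reviews are triggered by 3-month completion and are interim monitoring, not a final report.

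A reader might infer more than the text supports:
- That the trial discards these data. They are collected; they are only assigned to no report.
- That the acceptability aim suffers equally. DTG satisfaction is reported at 6 months, and utilization reports at study end cover each participant.
- That people who got worse on BWW stay out of the extension. The documents say only that extension participants are self-selected; people who are still unwell might equally opt in.
- That upper bounds for events never seen would measure the loss. Most Table 2 events are unlikely to have zero counts. Death, the plausible exception, depends on optional consent to data linkage, so survey completers are not its denominator.
- That the plan errs in having no DTG before-after display of RAS-r, PHQ-9 and GAD-7. Such a display is a matter of preference.

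**Conclusion.** The point holds for adverse events. As written, events during DTG's only exposed period enter no stated report, and about 26–33 % of planned first exposures to BWW are missing from the safety description.

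One third is the upper end of that range and follows directly from the 2:1 ratio. The lower end assumes that 30 % of DTG is lost before crossover while no ITG participant is removed from the count. Exposure here means scheduled access: the documents do not say how many will log in, or whether those who miss the 3-month survey will still take up BWW.

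The consequence is modest. The randomized 3-month comparison of ITG with DTG, the extension comparison and the power calculation are unaffected.

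**What to change.** Amend the adverse-event sentence in the section on primary and secondary analyses so that 6-month events are also reported descriptively for DTG (months 4–6, on BWW) beside DTG months 0–3 (no BWW). Add a pooled first-exposure table combining ITG months 0–3 with DTG months 4–6. Label both as non-randomized and without a concurrent control. Align the Adverse events section so that the two places name the same groups, and state there whether the extension group means ITG-e alone or both re-randomized groups.

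Reported first exposures would rise from about 667 to about 1000 as randomized, or from about 467 to about 700 with 30 % attrition in both arms and no further loss after month 3. The cost is two wording changes and some extra tables from data already scheduled. The drawback is that these tables cannot separate an effect of BWW from natural fluctuation, and the text should say so.

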### Study setting

This study is based in Ontario, Canada’s most populous province. In Ontario, all physician and hospital mental health care, including outpatient services located in hospitals, are publicly funded under the single-payer provincial health insurance plan [20]. Subsidized community services offer some services for free or at a low cost. [20] There is also a large network of private inter-professional health providers including social workers, psychologists and registered psychotherapists who provide counselling and psychotherapy for a fee [21]. Third party insurers may offer partial or limited coverage for these services [22]. Due to limited publicly funded services and high costs for private services, public programs have long wait times on the order of months to a year or more, and often provide time-limited treatment only [23, 24]. Although the potential for virtual mental health care platforms within this resource constrained system is apparent, few widely accessible platforms exist, and none with sufficient evidence to warrant their wide scale adoption into clinical practice.

Within Ontario, three test sites were selected from cities with populations of approximately 80,000, 150,000, and 2.5 million. These sites include: 1) a community general hospital with inpatient and outpatient mental health services and an emergency department (ED) that sees a high volume of mental health-related visits, 2) a psychiatric hospital with inpatient and outpatient mental health services, and 3) an academic ambulatory care hospital with a large outpatient mental health program. With the exception of the ED, the majority of the clinical programs accept referrals from the community or from within their respective hospital for assessment and management of chronic and/or treatment refractory mental health problems. The third site offers self-referral to some of the treatment programs with the requirement that individuals undergo an extensive intake assessment prior to being formally accepted to the waitlist.

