#### Outcome measures

##### Primary and secondary outcomes

The primary outcome is the total score on the Recovery Assessment Scale-revised (RAS-r) at 3 months. The RAS-r is a 24-item validated pan-diagnostic consumer-oriented outcome measure [31]. All items are scored on a 5-point scale from ‘strongly disagree’ to ‘strongly agree.’ The choice of the RAS-r reflects the current “recovery era” for mental health policy and services and the increasing focus on consumer achievement of satisfying and fulfilling lives, rather than being symptom free [31]. Secondary outcomes include the five subscale scores of the RAS-r: 1) personal confidence and hope, 2) willingness to ask for help, 3) goal and success orientation, 4) reliance on others, and 5) not dominated by symptoms; symptoms of depression and anxiety measured with the Personal Health Questionnaire-9 item (PHQ-9) and the Generalized Anxiety Disorder Questionnaire-7 item (GAD-7) respectively; quality of life measured with the EuroQOL group’s EQ-5D-5 L [32]; and community integration assessed with the Community Integration Questionnaire (CIQ) [33]. The 15-item CIQ is a brief, reliable measure of a person’s level of integration into the home and community. The overall score ranges from 0 to 29 with a higher score indicating better integration. The CIQ can also be divided into 3 subscales: 1) home integration, 2) social integration, and 3) productivity [33]. Timing of the completion of outcome assessments is outlined in Table 1.

**Table 1 Tab1:** Timing of outcome assessments

Measures/Assessments	Baseline	3 months	6 months
RAS-r	X	X	X
PHQ-9	X	X	X
GAD-7	X	X	X
CIQ	X	X	X
EQ-5D-5 L	X	X	X
Adapted CSRI^a^	X	X	X
Out-of-pocket costs^b^	X	X	X
Health Administrative Data	N/A	X	X
BWW satisfaction	N/A	X (ITG)	X (DTG)

*RAS-r* recovery assessment scale-revised, *PHQ-9* personal health questionnaire, 9-item, *GAD-7* generalized anxiety disorder questionnaire, 7-item, *CIQ* community integration questionnaire, *EQ-5D-5 L* Euro-QOL quality of life measure, *CSRI* client service receipt inventory, *BWW* big white wall, *ITG* immediate treatment group, *DTG* delayed treatment group, *N/A* not assessed

^a^Adapted for the Ontario health care context

^b^Includes costs for medication, laboratory investigations, mental health services, and physical health services

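### Randomization is stratified by site and recruitment setting, but neither version of the primary ANCOVA includes site and neither is named as decisive: a small, avoidable loss of precision, not a bias

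*Protocol article*

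**What the plan says.** Under Allocation and blinding, the protocol article states: "Randomization sequences will be generated independently and will be stratified by site and recruitment setting". The same section sets the ratio: "At enrollment, a 2:1 allocation ratio will be used to randomize participants to ITG or DTG". Study setting describes three dissimilar hospitals (a community general hospital with an emergency department, a psychiatric hospital and an academic ambulatory hospital): "three test sites were selected from cities with populations of approximately 80,000, 150,000, and 2.5 million".

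The outcome is fixed under Primary and secondary outcomes: "The primary outcome is the total score on the Recovery Assessment Scale-revised (RAS-r) at 3 months". Its analysis, under Primary and secondary analyses, is intent-to-treat "using an ANCOVA controlling for baseline RAS-r score as well as treatment group", and this is to be done "unadjusted and adjusted for baseline PHQ-9, baseline GAD-7, age, sex, education, relationship status, household income, duration of episode, and recruitment setting". That is a complete list of nine covariates. Recruitment setting is on it; site is not.

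The same section extends the specification: "The same analysis will be repeated for all secondary outcomes at 3 months controlling for baseline score and treatment group". The 6-month comparison in the extension subset follows the same description, with the 3-month score added. For attrition: "In sensitivity analysis, we will repeat this using a marginal structural model to account for attrition"; the variables behind its weights are not listed. Both models under Exploratory analyses list recruitment setting without site.

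No sentence says whether the unadjusted or the adjusted ANCOVA decides the trial, or how a disagreement between them would be read.

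**The concern.** Stratified allocation balances the arms within each stratum, so differences between strata largely drop out of the treatment contrast. A model that omits the strata still leaves those differences in its error term. The reported standard error is then larger than the true sampling error of the estimate, the test runs below its nominal level, and some power that the design has already secured is given away. Site is the clearer omission because it appears in neither version, and the three hospitals could plausibly differ in mean recovery score.

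The second issue is uniqueness. With two versions of the primary ANCOVA and no lead named, two p-values could be offered for one hypothesis. What is at stake is a little precision and an unambiguous primary result, not the validity of the estimate.

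**Working it through.** **Inputs from the protocol article (Power calculation).** 1000 recruited, 30% attrition, so 1000 × 0.7 = 700 analysed; 2:1 allocation, so about 466.7 and 233.3; alpha 0.05 (two-sided assumed, as sidedness is not stated); power 0.9; baseline to follow-up correlation 0.8; detectable difference 1.35.

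**Step 1, the plan's own figure.** Detectable difference = (1.960 + 1.282) × SD × √(1 − 0.8²) × √(1/233.3 + 1/466.7) = 3.2415 × SD × 0.6 × 0.0802 = 0.156 × SD. No RAS-r SD is given, so 1.35 cannot be checked independently. It implies SD = 1.35 / 0.156 = 8.66 and a residual SD of 0.6 × 8.66 = 5.19. With these values the statement is self-consistent.

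**Step 2, site alone.** Let R² be the share of residual variance explained by site. The document gives no value, so a range is assumed.
- Detectable difference with site in the model: 1.35 × √(1 − R²).
- Power at 1.35 with site: Φ(3.2415/√(1 − R²) − 1.960).
- Excess of the model standard error without site: 1/√(1 − R²) − 1.
- Actual level of the nominal 5% test without site: 2 × [1 − Φ(1.960/√(1 − R²))].

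| Assumed R² of site | Detectable difference with site | Power with site (nominal 0.900 without) | SE excess without site | Actual level without site |
|---|---|---|---|---|
| 1% | 1.343 | 0.903 | 0.5% | 4.9% |
| 2% | 1.336 | 0.906 | 1.0% | 4.8% |
| 5% | 1.316 | 0.914 | 2.6% | 4.4% |
| 10% | 1.281 | 0.927 | 5.4% | 3.9% |

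The power column is measured against the nominal 0.900. Under stratified allocation the test without site already has slightly more than that, Φ(1.2816/√(1 − R²)): 0.902 at 2% and 0.912 at 10%. The gain actually realised at 10% is therefore 0.927 − 0.912, about 1.6 points.

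**Step 3, simulation of the design.** N = 700, 3 sites × 4 settings, stratified 2:1 blocks of 6, residual SD 5.19, 4000 runs per row. Monte Carlo error is about 0.3 points for type I error and 0.5 for power. Site shares, number of settings and all R² values are assumptions. Entries are unadjusted / adjusted without site / adjusted plus site.

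| R² of site, setting, other covariates | Type I error | Power at 1.35 | Type I error if either stated version counts |
|---|---|---|---|
| 0, 0, 5% | 0.049 / 0.049 / 0.049 | 0.899 / 0.907 / 0.907 | 0.061 |
| 1%, 1%, 5% | 0.045 / 0.044 / 0.045 | 0.902 / 0.916 / 0.916 | 0.056 |
| 2%, 2%, 10% | 0.045 / 0.045 / 0.047 | 0.906 / 0.929 / 0.932 | 0.059 |
| 5%, 5%, 10% | 0.033 / 0.042 / 0.047 | 0.910 / 0.941 / 0.950 | 0.051 |
| 10%, 10%, 10% | 0.028 / 0.035 / 0.050 | 0.922 / 0.956 / 0.965 | 0.043 |

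With strong strata the stated models run at about 3-4%, and adding site restores about 5%. Over the stated adjusted model, adding site gains 1 power point or less. At a true difference of 1.35, the two stated versions reached different conclusions in about 3-5% of trials.

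**Step 4, two versions.** Treating both tests as exact 5% tests with correlation √(1 − R²) gives an either-test error of 6.0%, 6.5% and 7.1% when the covariates explain 5%, 10% and 20% of residual variance. That ignores the conservatism in Step 3. Allowing for it, the last column gives 4.3-6.1%. Further runs of 6000 each gave 4.7-6.2%. Across the values tried, about 4-6.5% is a fair range.

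**The case against.** Four points can be made for the plan.

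- **The effect is small and in the safe direction.** This stands. Omitting site makes the test conservative and does not distort the estimate.
- **Recruitment setting may already carry much of site.** This stands in part. The Recruitment section lists clinics without assigning them to hospitals, and the coding of setting is not given. If it is coded by clinic, it would absorb part or most of site. All three hospitals have outpatient services, however, so a broad outpatient category would span sites.
- **The choice of lead model and stratum terms belongs in the analysis plan, which is not shown.** This does not remove the point. The article sets out its covariates one by one, includes one of its two stratification factors and leaves out the other.
- **The baseline-only model could be the lead, because the power calculation rests on it.** That is plausible, but the text does not say so, and that version omits both factors.

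A reader might also infer more than the document supports. One stronger reading is that two primary p-values raise the false-positive rate to 6-7%. No sentence says that either result suffices, and the upper figure needs two exact 5% tests and covariates that explain 20% of what remains after a baseline correlated at 0.8. Another is that standard errors would shrink by 1.0-5.1%, from an assumed R² of 2-10% for site and setting together. That credits recruitment setting, which the adjusted model already has. A third is that site is absent from every analysis. This cannot be known for the marginal structural model, whose weight variables are not listed.

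**Conclusion.** The point holds as a modest mismatch between randomization and analysis. Site is absent from both versions of the primary ANCOVA and from the secondary and 6-month analyses built on them; recruitment setting is absent from the unadjusted version. Under the assumed R² values, leaving out site costs under 1 power point at 1-2% of residual variance and about 3 points at 10% against the nominal 0.90, with a smaller gain over what the stated models would actually achieve. It costs nothing if site explains nothing. The missing designation of a lead version is a real ambiguity, but its effect on type I error is small and of uncertain direction. Neither issue threatens the validity of the treatment estimate. The reason to act is that the correction costs almost nothing.

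**What to change.** Name one primary analysis: an ANCOVA of 3-month RAS-r on treatment, baseline RAS-r, site and recruitment setting, pooling very small cells, with the other listed covariates included if wanted. Label the other version supportive and keep site and setting in it. Use the same terms for the secondary outcomes. In the 6-month extension model add site, and keep setting in both versions (the adjusted one already has it). State how recruitment setting is coded.

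The cost is a sentence or two of analysis wording and a few degrees of freedom out of about 700. Site is already known because it is used to randomize. Trial status reports 475 participants consented against a minimum target of 1000, and the 3-month analysis waits for all 3-month data, so as of the article the change could be made without sight of outcome comparisons.
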